#### Secondary outcome measures

##### *Pharmacoeconomic secondary outcome measures*

Incremental cost utility ratio at 6 months (time frame: 6 months)

This outcome will be calculated as the average differential cost per patient between both study arms (mean costs of the SinnoTest® arm − mean costs of the control arm) divided by the difference in effectiveness between both study arms measured in the number of years of life weighted by the quality of life (QALY: quality-adjusted life year) generated by each of the strategies (mean QALY of the SinnoTest® arm − mean QALY of the Control Arm).

QALY will be measured using the EuroQol-5D-5L. The Spanish value set will be used to obtain the EQ-5D index values. Cost will be considered from a Societal perspective, including both direct and indirect costs The ratio will be expressed in cost (2019 Euros) per QALY earned, which represents the additional cost that will have to be spent to earn a healthy year of life.

As direct costs, we will consider concomitant medications, procedures, outpatient consultations (both primary and specialized care), hospitalizations, and complementary test (laboratory, radiology…). Regarding indirect costs, we will consider sickness absences, transportation, home assistance (both by professional and non-professional caregivers), and home modifications related to the disease.

Regarding the determination of unit costs, we will favor, where possible, a cost-of-production approach:

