##### *Pharmacoeconomic secondary outcome measures*

Incremental cost utility ratio at 6 months

The statistical analysis will proceed as follows:

Calculating the 6-month incremental cost-utility ratio from the community perspective using the following parameters: difference of the averaged total cost per patient and difference in the average number of QALYs generated by the strategies on both study arms. The ratio will be expressed in cost per QALY earned, which represents the additional cost that will have to be spent to earn a healthy year of life.QALYs will be calculated from the answers provided by EQ5D-5L, based on a weighting system reflecting preferences on the health status of the general Spanish population (41). The EQ5D questionnaire will be filled in by the patient at the inclusion visit and then at M3 and M6. The QALYs will be calculated by the area under the curve assuming a linear evolution of the quality of life between the measurement times. The average number of QALYs will be calculated for each of the strategies under study.In case of missing data, multiple imputation techniques will be carried out, in addition to sensitivity analysis, with the objective of checking that the assumptions made in the imputation were correct, and checking whether the conclusions of the study are modified, or not, according to the analysis strategy adopted.Although subjects will be followed up to 12 months, ICER will only be calculated at 6 months: as pointed out, according to the EULAR recommendations for biotherapy management in rheumatoid arthritis [25], 6 months is the time to assess if the therapeutic objectives of the medication has been achieved (remission or at least low disease activity). Based on those recommendations, if the patient is still active, treatment should be modified.Sensitivity analysis: Deterministic sensitivity analysis: it allows to take into account the uncertainty on certain parameters that can influence the cost of the strategies. We will consider the best and worst scenarios. Taking into account the variability in direct cost associated with treatment in RA [29], we will consider a ± 20% cost increase/decrease. This analysis will take into account in particular the impact of the cost of SinnoTest®, the impact of a change in the cost of treatments through biotherapy, the impact of the cost of work stoppages and the time of the caregivers, and probabilistic sensitivity analysis: it will include the calculation of the confidence intervals of the cost-utility ratio by the nonparametric Bootstrap method and the plot of the associated acceptability curve.In addition to the cost-utility ratio, differences in cost and utility will be analyzed separately: Comparison of the cost of the two strategies: the difference in costs between the groups will be tested by a Student test or a nonparametric test (Mann-Whitney tests) in case of non-Gaussian distribution. The choice of the test will be made with regard to the distribution of costs in each group (Shapiro-Wilk test, on raw data or, if necessary, on transformed data. In addition, distribution will also be assessed using histograms). The construction of the average cost confidence interval will be based on the nonparametric Bootstrap method and comparison of the utility: The number of QALYs will be calculated taking into account the time elapsed between two successive measurements. If the initial utility level between the groups differs (> 10%), a comparison of the number of QALYs between the groups will be made from a linear model to adjust for this level of utility [30]. Given the time horizon, no updates will be made; those of the inclusion visit (M0) will be taken.Multivariable linear regression method will be used to determine the explanatory factors of the average cost per patient of the strategies (i.e., age, sex, socio-professional category). In a first step, bivariable analysis will be carried out. Those variables with a *p* value < 0.15, plus age and gender, will be included in the multivariable analysis. Different models will be compared using the Akaike Information Criteria.

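### The separate cost comparison can switch to Mann-Whitney, which does not test the difference in mean cost that the ICUR and ICER use

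*Protocol article*

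**What the plan says.** Under Outcomes {12}, the ICUR numerator is the "average differential cost per patient between both study arms", spelled out as "mean costs of the SinnoTest® arm − mean costs of the control arm". The ICER at 6 months is defined with the same numerator. Under Statistical methods {20a}, the ICUR inputs are again the "difference of the averaged total cost per patient and difference in the average number of QALYs generated by the strategies on both study arms". All three places mean a difference in arithmetic means.

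The same {20a} section then adds a separate comparison of costs: "the difference in costs between the groups will be tested by a Student test or a nonparametric test (Mann-Whitney tests", the latter when costs are non-Gaussian. Normality is judged within each arm ("Shapiro-Wilk test, on raw data or, if necessary, on transformed data"), and histograms are a further check. The interval for average cost is to come from a non-parametric bootstrap, as is the interval for the cost-utility ratio, with an acceptability curve.

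**The concern.** The test changes its target with the data. On raw costs, Student's test addresses the difference in arithmetic means. Mann-Whitney addresses whether a patient in one arm tends to cost more than a patient in the other. These two questions agree only under restrictive conditions, such as distributions of the same shape.

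The Mann-Whitney branch is the likely one. The cost items in {12} include hospitalisations, sickness absence, home assistance and home modifications. Such items are nil for many patients and large for a few, so right skew is a reasonable expectation. Unequal shapes between arms are plausible too. The SinnoTest arm bears the test's cost and draws mainly on three drugs, while the control arm may use any bDMARD. The Background also expects fewer hospitalisations and less work stoppage.

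At stake is a cost p-value that disagrees with the bootstrap interval printed beside it. The protocol gives no rule for which one then describes the cost result.

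**Working it through.** **The plan's own figure.** The only sample size given is 90 per group, for 65% against 83.2% response (65% + 18.2 points), two-sided 5%, power 80%. With pooled proportion 0.741:

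n = [1.960·√(2·0.741·0.259) + 0.842·√(0.65·0.35 + 0.832·0.168)]² / 0.182² = 89.8, so 90.

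It reproduces. It concerns response, not cost; the protocol gives no cost mean, spread or distribution. From here, 90 per arm is the protocol's figure and the cost distributions are assumptions.

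**Why ranks and means part company.** A lognormal cost with mean m and log-SD s has median m·exp(−s²/2). Take equal means of 6,000 with s = 0.5 in one arm and 0.8 in the other:

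- Medians: 6,000·exp(−0.125) = 5,295 and 6,000·exp(−0.32) = 4,357.
- Probability that a patient in the first arm costs more than one in the second: Φ[(0.32 − 0.125)/√(0.25 + 0.64)] = Φ(0.207) = 0.58.

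Without ties, the Mann-Whitney null requires 0.50. Mean costs are identical, yet Mann-Whitney has a true departure to detect.

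**Rejection at two-sided 5%, 90 per arm, equal true means**

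| Assumed costs | Mann-Whitney | t on raw costs |
|---|---|---|
| Lognormal, log-SD 0.6 / 0.6 | 5.1% | 5.4% |
| Lognormal, CV 1.0 / 1.0 | 5.2% | 5.7% |
| Higher routine cost, fewer expensive events: three mixtures | 5.0%, 11%, 15% | 4.4% in the latter two |
| Lognormal, CV 1.0 / 0.75 | 17.6% | 5.3% |
| Lognormal, log-SD 0.5 / 0.7 | 25% | 5.4% |
| Lognormal, log-SD 0.8 / 1.0 | 27% | 5.3% |
| Lognormal, log-SD 0.5 / 0.8 | 47% | 5.8% |
| Lognormal, CV 1.0 / 0.5 | 60.7% | 6.0% |
| Lognormal, log-SD 0.6 / 1.0 | 71% | 6.1% |
| Lognormal, log-SD 0.5 / 1.0 | 86% | 6.9% |

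The CV rows use a mean of 8,000 and the log-SD rows 6,000. The level does not affect the lognormal results, because both arms share it. The 11% mixture has control costs of 5,000 + 20%·6,000 = 6,200 and SinnoTest costs of 5,600 + 10%·6,000 = 6,200, so its means are equal by construction.

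**How often the switch is triggered.** Shapiro-Wilk rejected normality of raw costs in at least one arm in 100% of these simulated trials.

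**The opposite error.** With equal medians but unequal means:

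- Log-SD 0.5 / 0.8: means differ by exp[(0.64 − 0.25)/2] = 1.22, i.e. 22%. Mann-Whitney rejects in 5.1%, raw t in 35%.
- Log-SD 0.5 / 1.0: means differ by exp[(1.00 − 0.25)/2] = 1.45, i.e. 45%. Mann-Whitney rejects in 5.9%, raw t in 66%.

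**The case against.** The test is supplementary. The protocol presents it as an addition to the cost-utility ratio, and its only economic gate, whether to run the budget impact analysis, depends on cost-effectiveness rather than on a significant cost difference. A reader would also see mean costs and a bootstrap interval. All of this stands, and it limits the point to one p-value.

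Several stronger readings are tempting but unsupported:

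- **That the ICUR and ICER are compromised.** They use mean costs, and their probabilistic uncertainty does not pass through the normality check or Mann-Whitney.
- **That the plan prescribes a t-test on log costs.** Transformation is mentioned only within the description of the Shapiro-Wilk check. A test on the transformed scale is a natural consequence, but it is not stated.
- **That Shapiro-Wilk alone decides.** Histograms also inform the choice, so rejection in every simulated trial does not prove that Mann-Whitney would always be used.
- **That the false-positive rate is 60% or more.** That needs a very large difference in spread at equal means. With equal shapes Mann-Whitney keeps its level, and in mixtures resembling this intervention it gave 5% to 15%.
- **That the protocol itself expects the cost distribution to change shape.** It expects reductions in resource use and lost production. Unequal shape is an inference from the design.

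What survives is that a stated rule sends non-Gaussian costs to a test of a different quantity.

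**Conclusion.** The concern holds for the separate between-arm cost test and for nothing beyond it. This is a stated choice aimed at the wrong quantity, not a detail left to a later document. With equal means, Mann-Whitney rejects in about 5% of trials (same shape, or some mixtures), 11–18% under moderate shape differences and about 60% or more under extreme ones, with values between for intermediate cases. The raw-scale t-test stays at about 4–7% throughout. These sizes rest on assumed cost distributions and vary widely with them. The mismatch between Mann-Whitney and a difference in means does not depend on those assumptions. The point should be corrected, but it does not threaten the economic estimates.

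**What to change.** In the cost comparison under {20a}, remove the normality-driven choice of test and the Mann-Whitney test for costs, and state that costs will not be tested on a transformed scale. Compare arithmetic mean costs on the raw scale whatever the distribution looks like. Use the non-parametric bootstrap already planned, and say explicitly that it is applied to the between-arm difference in mean cost, since the text now speaks only of an interval for average cost. A Welch t-test or a regression on raw costs with robust standard errors would also do. Report that same difference as the numerator of the ICUR and ICER. Shapiro-Wilk and histograms can stay as description. The cost is a few lines of wording; no new data, visits or patients are needed.

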The prices of drugs dispensable through pharmacies will be obtained from the Database of the Spanish Official College of PharmacistsThe prices of hospital dispensing drugs will be obtained from the Pharmacy Services of each participating center.The costs of the different medical acts (first visits or revisions, in primary or specialized care, by different medical professionals) will be provided by each participating center.The costs of hospitalizations and the procedures that are carried out will be provided by each participating center.The costs of the complementary tests will be obtained from each participating center.The use of home assistance will be evaluated based on a standard average cost. The cost of employing professionals from the medico-social sector (for example, occupational therapist) will be estimated based on an average cost per hour.The cost of improvements in the home will be estimated, as far as possible, in the billing data or in the data obtained by the professionals of the sector involved.In relation to the costs of caregivers (non-professionals) and the loss of production of the patient, according to the recommendations, the direct costs will take into account the time of the people intervened and the time that the caregivers dedicate to the care of the patients. However, in relation to the valuation method, there is no agreement on the method to be used. We will favor the human capital method, where the “value” of an individual is estimated by its productive value in the labor market, that is, through the gross salary. These productive costs will be obtained through the data of age, sex, and professional sector of the individual through the national statistics available on the Spanish Social Security website.The cost of medical transport will be assessed through the rates established based on the distance and type of vehicle.

We consider that 6 months is enough time to assess the performance of the intervention. According to the EULAR recommendations for biotherapy management in rheumatoid arthritis [25], 6 months is the time to assess if the therapeutic objectives of the medication has been achieved (remission or at least low disease activity). Based on those recommendations, if the patient is still active, treatment should be modified.

Incremental cost-effectiveness ratio at 6 months (time frame: 6 months)

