#### Implementation {16c}

The eligible patient will be randomized, with a 1:1 allocation, via an internet server (access by secure code 24/24; RedCap) in one of two groups: SinnoTest group or control group. A blood sample will be extracted from the patient randomized in the software arm for the determination of selected biomarkers for the use of SinnoTest®. A patient randomized to the control arm will also have his/her blood drawn (but this one will not be analyzed) so that the two arms are identical and to maintain blinding for the patient.

The coordinating center will manage its development and its availability on the internet. It will only be done after informing the patient and signing the consent. The randomization will be individual with blocks of random size, stratified by center. The investigator or CRA will connect to the server after confirming that the patient meets all the inclusion/exclusion criteria. Block randomization will ensure that an equal number of patients are randomized to each study arm and to each study site.

The involvement of 5 centers in this study allows individual randomization without fear of the existence of a contamination bias. Indeed, investigators may change their empirical management under study because of patient outcomes previously included with SinnoTest®, but the relatively low inclusion counts per center suggest that this bias will be negligible. In addition, in the control arm, the treatments will be prescribed by the rheumatologist who usually treats the patient, so the number of patients who will have the opportunity to “learn” is even lower, because it is shared among all doctors that include patients in the study.

This design also neutralizes the disappointment bias of investigators who can all use the innovation under study. By stratifying by center, about half the patients will have their treatment prescribed by SinnoTest, so they can be sure they will have the opportunity to use the software and assess its functions.

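### The cost comparison ignores centre, the factor used to stratify randomisation, so its test overstates the standard error and is conservative; the gain from adjusting is free but probably small

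*Protocol article*

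**What the plan says.** All references are to the protocol article.

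- **Cost test.** Under Statistical methods, Pharmacoeconomic secondary outcome measures: "the difference in costs between the groups will be tested by a Student test or a nonparametric test". The choice between the Student and Mann-Whitney tests follows the cost distribution, judged by Shapiro-Wilk test and histograms. No covariate or stratum is mentioned.
- **Cost interval.** Same section: "The construction of the average cost confidence interval will be based on the nonparametric Bootstrap method". The resampling scheme is not described.
- **Randomisation.** Implementation {16c}: "The eligible patient will be randomized, with a 1:1 allocation", and "The randomization will be individual with blocks of random size, stratified by center". There are five centres.
- **Prices taken from each centre.** Outcomes {12}: "The costs of hospitalizations and the procedures that are carried out will be provided by each participating center"; "The costs of the complementary tests will be obtained from each participating center". Hospital-dispensed drugs and medical visits are also priced by the centre.
- **Prices from common sources.** Same list: "The use of home assistance will be evaluated based on a standard average cost". Drugs dispensed through pharmacies come from one national database, production losses and unpaid care from national salary statistics, and medical transport from set rates.
- **Other cost models.** The multivariable cost regressions in the same statistical section and under Methods for additional analyses {20b} look for explanatory factors and factor-by-arm interactions. The factors they name are demographic or clinical. They do not replace the arm comparison.

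**The concern.** When allocation is balanced within centre, a cost level that is high or low throughout a centre affects both arms about equally and largely cancels from the difference in means. A two-sample test does not use this. Its standard error is built from the total variance, including the between-centre part that has already cancelled. Pricing by centre makes such a part plausible, since identical resource use can receive a different cost at another hospital.

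At stake is precision. The cost difference is the numerator of both the cost-utility and the cost-effectiveness ratio. Objectives {7} counts pharmacoeconomic impact at 6 months among the primary aims, and Outcomes {12} makes the budget impact analysis conditional on the software being found cost-effective. The clinical comparisons in the same plan are regression models adjusted for baseline variables; the stated cost comparison alone has no adjustment.

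**Working it through.** **The plan's own figure.** Sample size {14} gives 90 per group for 65% against 83.2%, two-sided 5%, 80% power. With pooled variance and no continuity correction:

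n = [1.96·√(2·0.741·0.259) + 0.8416·√(0.65·0.35 + 0.832·0.168)]² / 0.182² = 89.8, so 90 per arm (power 80.1%).

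The figure reproduces. It concerns response. No standard deviation, detectable difference or power is stated for costs, so what follows rests on assumed ranges.

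**Step 1: general formula.** Let rho be the share of cost variance between centres. With 1:1 blocks within centre, the true standard error of the arm difference is close to σ_within·√(2/n). The unadjusted t-test estimates σ_total·√(2/n). The ratio is k = 1/√(1 − rho).

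- Actual two-sided error of the nominal 5% test: 2·[1 − Φ(1.96·k)].
- Power, for a difference that the centre-adjusted analysis detects with 80%: Φ(1.96 + 0.8416 − 1.96·k).

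| rho (assumed) | SE ratio k | Actual type I error | Power |
|---|---|---|---|
| 0.02 | 1.010 | 0.048 | 79.4% |
| 0.05 | 1.026 | 0.044 | 78.5% |
| 0.10 | 1.054 | 0.039 | 76.9% |
| 0.20 | 1.118 | 0.028 | 72.9% |
| 0.30 | 1.195 | 0.019 | 67.7% |

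**Step 2: simulation check.** Five centres, 180 patients, blocks of 2, 4 or 6 (assumed sizes), 4,000 runs per setting. At rho 0.20, in within-centre SD units:

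- True SD of the cost difference 0.147; SE reported by the t-test 0.167; SE from the arm-plus-centre model 0.149 (theory: √(2/90) = 0.149).
- Type I error 0.024 for both the t-test and Mann-Whitney, 0.046 for the adjusted model.
- Power 71.8% for the t-test, 79.3% adjusted.
- With unequal centres (80/40/30/20/10): type I error 0.023 unadjusted, 0.045 adjusted.
- At rho 0 the t-test and the adjusted model agree.

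With skewed (lognormal) errors at rho 0.20 the t-test behaves the same way: type I error 0.025 and power 74.0%, against 0.046 and 80.5% adjusted. Mann-Whitney had type I error 0.020 but 90.8% power for a pure shift. The power loss is thus a statement about the t-test; the rank test does not estimate the mean cost difference that the ratios need.

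**Step 3: plausible size of rho.** Let s be the share of cost that is centre-priced, c the between-centre coefficient of variation (CV) of price, and w the within-centre CV of cost. For five centres:

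rho/(1 − rho) = (4/5)·(s·c)² / {w²·[1 + (s·c)²]}, and k = √[1 + rho/(1 − rho)].

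None of s, c and w is in the document.

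| s | c | w | Excess SE |
|---|---|---|---|
| 0.5 | 10% | 60% to 40% | 0.3% to 0.6% |
| 0.5 | 20% | 60% to 40% | 1.1% to 2.4% |
| 0.5 | 30% | 60% to 40% | 2.4% to 5.4% |
| 1 | 20% to 30% | 100% | 1.5% to 3.2% |
| 1 | 30% | 40% | 19% |

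For s = 0.5, c = 30%, w = 40%: 0.8·0.0225/(0.16·1.0225) = 0.110, and √1.110 = 1.054. The 19% in the last row requires every cost item to be centre-priced, a wide price spread and a small patient-to-patient spread, all together.

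**The case against.** The case for leaving the plan alone has four parts.

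- **No wrong conclusion follows.** A reader might infer that centre prices bias the cost difference, raise its true sampling error or inflate the type I error. They do none of these. Stratification has already protected the contrast; only the estimated standard error is too large, and the ratio point estimates hardly change. This stands in full.
- **The effect may be small.** A reader might also take costs to differ between centres by construction, with losses approaching a fifth of the standard error. The document says that prices are obtained from each centre, not that they differ. The centres are tertiary hospitals in one region, and several societal cost items use common sources. This stands and limits the likely size.
- **The bootstrap is not shown to be wrong.** The article names only a nonparametric bootstrap. Resampling within arm and centre would fit that name, and such detail commonly sits in an analysis plan that is not at hand. This stands: the fault lies in the named test, and the bootstrap scheme is only something to align with the correction.
- **The consequence is limited.** The ratios are listed as secondary outcomes, the cost test is reported in addition to the ratio, and the sample size is built on response. The ±20% deterministic analysis already varies costs. This stands in part: that analysis shifts the level of costs, not the spread between centres, so it does not answer the point.

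Silence is no defence for the test itself. The article fixes it and the rule for choosing it, and a two-sample test has no place for centre.

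**Conclusion.** The point holds as a matter of efficiency. The stated cost test ignores the factor by which the trial randomises, counts between-centre cost variation as error, and so overstates the standard error and runs below its nominal level. The overstatement is about 1% at rho 0.02, 3% at 0.05, 5% at 0.10 and 12% at 0.20. If half of cost is centre-priced, with a price CV of 20% to 30% and a within-centre CV of 40% to 60%, it is about 1% to 5%. Low single digits are therefore the most probable range, but rho, the price spread and the centre-priced share are all assumptions. The correction is worth making because it costs nothing, not because the planned result would mislead.

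**What to change.** In the pharmacoeconomic statistical section, replace the two-sample test by a linear (or generalised linear) model of cost on arm and centre, report the centre-adjusted mean cost difference with its interval, and use that difference as the numerator of the cost-utility and cost-effectiveness ratios. State that bootstrap samples are drawn within arm and centre, so that the cost interval, the ratio intervals and the acceptability curve rest on the same estimate.

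Optionally, add a scenario that values all resource use with one common price list.

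The change is to analysis wording. It needs no new data, adds four centre parameters for 180 patients, and loses almost nothing if centres turn out not to differ. It should be settled before the cost data are compared by arm.

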### Sample size {14}

To re-evaluate the metrological properties of SinnoTest®, including 90 patients per group will highlight a differential response rate between the software arm and the control arm of more than 18.2%, considering a current response rate of 65% (defined as an EULAR good response [24]) with conventional care (control arm). The number of subjects required was estimated considering a bilateral alpha risk at 5% and a power of 80%. In total, 180 patients will be the estimated number of participants needed to achieve study objectives.

Due to the subject’s and the study’s characteristics, no allowance for loss to follow-up was considered in the sample size calculation: patients with a chronic disease, probably being followed up in the same center and by the same rheumatologist for some time (> 1 year), and the short follow-up time for the primary outcome.

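### The QALY comparison is adjusted for baseline utility only when the arms differ by more than 10%, and the cost-utility ratio is defined on unadjusted means, at a cost in precision and in robustness to chance imbalance

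*Protocol article*

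**What the plan says.** All of this is in the protocol article, mainly in the statistical methods under Pharmacoeconomic secondary outcome measures (Incremental cost utility ratio at 6 months).

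- **QALY construction.** EQ-5D is completed at M0, M3 and M6. "The QALYs will be calculated by the area under the curve assuming a linear evolution of the quality of life" between those times.
- **Ratio.** The denominator is the "difference in the average number of QALYs generated by the strategies on both study arms". The Outcomes section gives the same definition: mean QALY in one arm minus mean QALY in the other. Neither place mentions baseline utility.
- **Adjustment rule.** A separate item, presented as additional to the ratio, compares costs and utilities on their own. There, "If the initial utility level between the groups differs (> 10%), a comparison of the number of QALYs between the groups" will use a linear model that adjusts for the initial level. The text does not say whether 10% is relative to mean utility or an absolute 0.10.
- **Uncertainty of the ratio.** A nonparametric bootstrap interval and an acceptability curve are planned. Baseline utility is not mentioned for either.
- **Contrast.** In the same statistical section, the clinical secondary analysis adjusts 6-month EQ5D-5L for baseline variables without any condition.

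**The concern.** M0 utility is measured before treatment but is one of the three points that make up the QALY, and it predicts the other two. A chance difference at M0 therefore shifts the QALY difference in a known direction. The plan corrects for this only if the observed gap passes a threshold, so the data choose the estimator and gaps below the threshold are left alone. As written, the correction is tied to a side comparison and not to the ratio.

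The 6-month QALY difference is likely to be small, and it is the denominator of the ratio. Noise there widens the interval and flattens the acceptability curve. The Objectives section places pharmacoeconomic impact among the primary objectives, although the ratio is listed as a secondary outcome. The Outcomes section makes the budget impact analysis depend on the tool being judged cost-effective.

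**Working it through.** **Inputs from the protocol.** The Sample size section gives "including 90 patients per group". Implementation {16c} gives 1:1 allocation, stratified by centre. EQ-5D times are 0, 0.25 and 0.5 years.

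**Inputs assumed.** The protocol gives no utility mean, SD, correlation or expected gain. I take mean utility 0.5 to 0.7, SD (σ) 0.2 to 0.3 equal at all visits, and a common between-visit correlation ρ of 0.3 to 0.7. The central case is mean 0.6, SD 0.25, ρ 0.5.

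**Step 1. The protocol's own figure.** For 65% against 83.2% response, two-sided 5% alpha and 80% power, the pooled two-proportion formula without continuity correction gives 90 per arm (power 80.1%). The stated size is reproduced. It concerns response, and no QALY figure is stated that could be reproduced.

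**Step 2. Weight of M0.** The trapezoid gives QALY = 0.125·U0 + 0.25·U3 + 0.125·U6. M0 therefore carries 0.125/0.5 = 25% of the weight.

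**Step 3. Pass-through of a baseline gap.** The slope of QALY on U0 is 0.125 + 0.375ρ: 0.2375 at ρ 0.3, 0.3125 at ρ 0.5 and 0.3875 at ρ 0.7.

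**Step 4. How often the rule triggers.** The SE of the baseline difference is σ·√(2/90), or 0.0373 at SD 0.25. Reading 10% as relative to mean utility, P(|gap| > 0.10 × mean) is:

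| Mean utility | SD 0.20 | SD 0.25 | SD 0.30 |
|---|---|---|---|
| 0.5 | 9% | 18% | 26% |
| 0.6 | 4% | 11% | 18% |
| 0.7 | 2% | 6% | 12% |

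Read as an absolute 0.10, the rule triggers in about 0.1% (SD 0.20) to 2.5% (SD 0.30) of trials. Under either reading most trials stay unadjusted.

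**Step 5. What an unadjusted gap does (central case).**
- Gap just under the threshold: 0.06 × 0.3125 = 0.019 QALY (0.014 at ρ 0.3, 0.023 at ρ 0.7).
- Median absolute gap: 0.6745 × 0.0373 ≈ 0.025, and 0.025 × 0.3125 ≈ 0.008 QALY.
- For scale, a treatment gain of 0.05 at both M3 and M6 is worth 0.05 × 0.375 = 0.019 QALY. A gain of 0.10 is worth 0.0375.

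**Step 6. Precision.** Var(QALY) = σ²(0.09375 + 0.15625ρ), and R² = (0.125 + 0.375ρ)² / (0.09375 + 0.15625ρ). With SD 0.25 and 90 per arm:

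| ρ | R² (variance removed) | SE unadjusted | SE adjusted |
|---|---|---|---|
| 0.3 | 0.40 | 0.0140 | 0.0108 |
| 0.5 | 0.57 | 0.0155 | 0.0102 |
| 0.7 | 0.74 | 0.0168 | 0.0086 |

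**Step 7. Simulation of the rule (20,000 trials, no true effect, central case).** The SD of the estimated QALY difference is 0.0153 if never adjusted, 0.0131 under the conditional rule and 0.0101 if always adjusted. The two-sided 5% test rejects in 4.7%, 2.6% and 4.9% of trials respectively. Among trials where the rule does not trigger, the raw QALY difference still correlates 0.66 with the baseline gap. The conditional rule is therefore conservative, which costs power.

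**The case against.** The strongest defence is that nothing here is invalid. Allocation is randomised, so the raw QALY difference is unbiased over randomisation, and the conditional rule does not inflate type I error. The bootstrap resamples patients, so its interval already reflects chance baseline imbalance. All of this stands. It means the interval is honest on average. It does not correct for the imbalance seen in this trial, and it leaves the interval wider than it need be.

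Three stronger readings might be inferred, and the documents do not support them.

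- **That a baseline gap passes in full into the QALY difference.** The factor is 0.24 to 0.39.
- **That an uncorrected gap equals or reverses the treatment effect.** The match of 0.019 with 0.019 pairs the largest gap that escapes the rule, about 1.6 SE, with one assumed gain of 0.05. With the median gap, or a gain of 0.10, the shift is well below the effect. The protocol states no expected gain.
- **That a triggered adjustment is excluded from the ratio.** The article is silent on this. It sets the utility comparison beside the ratio and does not connect them, and a fuller analysis plan might do so.

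It can also be said that the baseline-adjusted EQ5D-5L analysis would make an imbalance visible. That is true, but it does not repair the ratio. It also shows the plan treating the same instrument in two ways.

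**Conclusion.** The point holds as one of efficiency and prespecification. The rule is stated in the document, is data-dependent, and leaves the QALY difference unadjusted in most trials: about 74% to 98% over the assumed grid with a relative 10%, and more if 10% is absolute. The consequence is conditional bias in the realised trial, by up to about 0.019 QALY in the central case and typically about 0.008, together with a variance that adjustment would cut by 40% to 74%.

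The direction follows from the protocol's own area-under-the-curve formula for any positive correlation between visits. The sizes rest on the assumed mean, SD, correlation and equal SDs. This is not systematic bias or an inflated error rate, and the sample size and primary response analysis are unaffected. It should be changed because pharmacoeconomic impact is a stated primary objective and the remedy uses data already collected.

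**What to change.** Delete the 10% trigger. State that the QALY difference will always be estimated by a prespecified linear regression of QALYs on arm, M0 utility and centre, centre being the stratification factor. State that this adjusted difference is the denominator of the cost-utility ratio, and that the regression is refitted in every bootstrap replicate so that the interval and the acceptability curve rest on the same estimate. The unadjusted difference can be reported alongside as descriptive.

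Table 1 already schedules EQ-5D at M0, so no new data, visits or patients are needed. The cost is a change of wording and a little extra analysis work.
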